#### 3.2 Primary endpoint

The primary outcome is the duration of dependency on vital organ support and intensive medical care, without censoring at 90 days. The duration of dependency on vital organ support

and intensive medical care will be reported as the crude number of ICU-stay days and as the time to live discharge from ICU, to account for mortality as competing risk. ICU non-survivors will be censored beyond the longest duration of ICU length of stay of the survivors. As the timing of ICU discharge to a regular ward may be affected by the availability of beds on regular wards, which could induce bias, we decided to analyze 'time to discharge from ICU' as 'time to *ready for* discharge from ICU'. A patient is considered 'ready for discharge' as soon as all clinical conditions for ICU discharge have been fulfilled (no longer in need for, or at risk of, vital organ support).

### 3.3 Secondary endpoints

- Glucose metrics in ICU: mean and median morning blood glucose concentrations; mean daily blood glucose concentration; incidence of moderate (40-70 mg/dl) and severe (<40 mg/dl) hypoglycemia during ICU stay; peak of blood glucose after correction of hypoglycemia; duration of hypoglycemia; number of hypoglycemic events per patient; minimum and maximum blood glucose concentration per day; time within blood glucose target range; blood glucose variability; hyperglycemic index. These parameters will be studied during ICU stay, with and without censoring at 90 days
- Mortality in ICU and in hospital, with and without censoring at 90 days
- Mortality 90 days post randomization
- Hospital length of stay, with and without censoring at 90 days
- Time to (live) discharge from hospital, with and without censoring at 90 days. Hospital non-survivors will be censored beyond the longest duration of hospital length of stay of the survivors.
- Time to final (live) weaning from mechanical respiratory support, with and without censoring at 90 days. ICU non-survivors will be censored beyond the longest duration of mechanical respiratory support of the survivors.
- The duration of ICU dependency (defined as the crude number of days with need for vital organ support and as the time to live discharge from ICU to account for death as competing risk), with censoring at 90 days
- The incidence of new infections during ICU stay, with and without censoring at 90 days. Two experts in infectious diseases, who will be blinded for study group assignment, will determine, in consensus, the presence of infection on admission to the ICU and the presence of infection acquired after randomization. They will make their decision on the basis of guidelines in the study protocol (see 13. Data handling).
- The need for tracheostomy during ICU stay, with and without censoring at 90 days
- Presence of clinical, electrophysiological and morphological signs of respiratory and peripheral muscle weakness during ICU stay in patient subgroups in selected centers, with and without censoring at 90 days

- New kidney injury during ICU stay, with and without censoring at 90 days: the presence or absence of new kidney injury during ICU according to modified KDIGO criteria (Kidney Disease: Improving Global Outcomes) (21, 22); proportion of patients in need of new initiation of renal replacement therapy in ICU; duration of renal replacement therapy in ICU; recovery from kidney injury
- The need for pharmacological or mechanical hemodynamic support during ICU stay and its duration, with and without censoring at 90 days. In addition, time to final (live) weaning from all pharmacological or mechanical support will be analyzed (with and without censoring at 90 days), with ICU non-survivors censored beyond the longest duration of pharmacological or mechanical hemodynamic support of the survivors.
- The incidence of new-onset atrial fibrillation and recurrence of pre-existing atrial fibrillation during ICU stay in selected centers, with and without censoring at 90 days. In order to quantify and phenotype burden of atrial fibrillation, we will perform a detailed analysis of atrial fibrillation occurrence, including timing of onset, duration and number of episodes. Strategies regarding medical and/or electrical rhythm control, as well as rate control will be documented.
- The incidence of major adverse cardiovascular events (MACE; non-fatal myocardial infarction, non-fatal stroke, low cardiac output syndrome, and cardiovascular death) during ICU stay in selected centers, with and without censoring at 90 days
- The presence or absence of signs of liver dysfunction in ICU, with and without censoring at 90 days: cholestatic liver dysfunction, cytolytic liver dysfunction.
- The duration of antibiotic treatment during ICU stay, with and without censoring at 90 days
- The incidence of bacteremia, airway, urinary tract, wound and other infections (all with and without censoring at 90 days).
- Inflammation: the effect of the intervention on markers of inflammation will be analyzed by comparing the distribution of the highest value of C-reactive protein during ICU stay and changes from baseline to the highest value and by comparing time profiles of daily C-reactive protein values (with and without censoring at 90 days).
- The number of readmissions to the ICU within 48 hours after discharge (with and without censoring at 90 days)
- The presence or absence of delirium during ICU stay (in selected centers), with and without censoring at 90 days. To that purpose, the worst Intensive Care Delirium Screening Checklist (ICSDC) score observed per day in ICU will be entered in the database.
- Biochemical, metabolic, immunological, endocrine, inflammatory, cardiac and (epi)genetic markers on blood and tissue samples up to 4 years post randomization (depending on additional funding and in selected centers)
- Muscle strength, rehabilitation, recovery of organ function and survival up to 4 years post randomization in selected centers and subgroups of patients (depending on additional funding)

- Long-term functional outcome:
  - o For all patients: a validated health questionnaire (Short Form 36, SF-36) 2 years  $\pm$  2 months after inclusion
  - o Subgroup of brain-injured patients (i.e. patients admitted because of traumatic brain injury, subarachnoid hemorrhage, intracranial bleeding, ischemic stroke or out-of-hospital cardiac arrest): additional functional outcome after 6( $\pm$ 1) and 12( $\pm$ 1) months (extended Glasgow outcome scale and/or modified Rankin scale)
- Use of intensive care resources (costs for hospitalization, for honoraria for medical and allied healthcare services, for pharmacy, for blood products, for clinical chemistry, for radiology, for graft products and for other expenses)

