|  | 
stay in patient subgroups in selected centers, with and without censoring at 90 days
 
 
- The presence or absence of new kidney injury during ICU stay, and duration and recovery herefrom, with and without censoring at 90 days
 
- The need for new initiation of renal replacement therapy in ICU (incidence, duration and recovery hereof), with and without censoring at 90 days
 
- The need for hemodynamic support during ICU stay, its duration and the time to (live) weaning from hemodynamic support, with and without censoring at 90 days
 
- The incidence of new-onset atrial fibrillation and recurrence of pre-existing atrial fibrillation during ICU stay in selected centers, with and without censoring at 90 days
 
- The incidence of major adverse cardiovascular events (MACE; non-fatal myocardial infarction, non-fatal stroke, low cardiac output syndrome, and cardiovascular death) during ICU stay in selected centers, with and without censoring at 90 days
 
- The presence or absence of signs of liver dysfunction in ICU, with and without censoring at 90 days
 
- The duration of antibiotic treatment during ICU stay, with and without censoring at 90 days
 
- The incidence of bacteremia, and of airway, urinary tract, wound and other infections acquired during ICU stay, with and without censoring at 90 days
 
- Peak and time profile of C-reactive protein concentrations during ICU stay, with and without censoring at 90 days
 
- The number of readmissions to the ICU within 48 hours after discharge, with and without censoring at 90 days
 
- The presence or absence of delirium during ICU stay (in selected centers), with and without censoring at 90 days
 
- Biochemical, metabolic, immunological, inflammatory, cardiac and (epi)genetic markers on blood and tissue samples up to 4 years post randomization (depending on additional funding and in selected centers)
 
- Muscle strength, rehabilitation, recovery of organ function and survival up to 4 years post randomization in selected centers and subgroups of patients (depending on additional funding)
 
- Long-term functional outcome:
 
 |

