| Strengths          | 
 
- Accurate glucose measurements, highly standardized
 
- Standardized protocol by extensively trained nurses, low incidence of hypoglycemia
 
 | 
 
- Multicenter
 
- Pragmatic, “real life” and thus not standardized context
 
                                                                                                        |
| Weaknesses         | 
 
- Nutritional strategy comprised the use of early parenteral nutrition, later shown to be harmful
 
                                                       | 
 
- Inaccurate glucose measurements
 
- Un-validated “if-then” algorithm, with <50% of measurements within target and high incidence of hypoglycemia
 
 |

 The performance of the protocol has been improved further by the LOGIC-Insulin software.

The **aim of TCG-fast** is to compare the effectiveness of TGC versus tolerating hyperglycemia in adult critically ill patients of both sexes **who are not receiving intravenous nutrition for up to one week in the ICU**. To this purpose, we will perform a multicenter RCT that is adequately powered for patient-centered and economic endpoints. Patients will be randomly allocated to TGC to target normal fasting glucose levels with insulin versus tolerating hyperglycemia up to a predefined level. TGC will be guided by our previously developed computer algorithm that has shown even to outcompete the well-trained nurses, with virtually preventing hypoglycemia (LOGIC-Insulin) (19). The efficacy and safety of the LOGIC-Insulin algorithm has been confirmed in a multicenter context by members of this consortium (20).

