## **8. Assessment of safety**

### **8.1 Notification of adverse events and serious adverse events**

Critical illness is a condition with adverse outcomes that are expected to occur. In this study adverse clinical outcomes are listed primary, secondary or safety endpoints. Hence, none of these study outcome endpoints will be considered as serious adverse events or suspected unexpected serious adverse reactions and thus do not need to be reported to the competent authorities. Any other and unexpected adverse reaction will be reported to the study sponsor.

For safety reasons, an interim analysis of hospital mortality will be performed after inclusion of 50% of the study population, with stopping boundaries predefined by the DMC to allow early study termination if the intervention group would appear clearly inferior.

The main adverse event of the intervention is hypoglycemia, which warrants prompt treatment. However, ICU physicians and nurses are familiar with the effects of insulin administration and follow-up of blood glucose concentrations. Hence, reporting hypoglycemic episodes to the competent authorities is not necessary. However, severe hypoglycemia (<40 mg/dl) that is resistant to intravenous glucose administration will be considered as a serious adverse event. This adverse event will be reported to the sponsor, after first knowledge. The immediate report will be followed by detailed, written reports. The sponsor will keep detailed records of all adverse events which are reported to him. These records will be submitted to the competent authorities when requested. In the intervention group, tight glucose control is timely stopped before ICU discharge, so that hypoglycemia provoked by the intervention is not expected to occur after ICU discharge. Therefore, hypoglycemia or other new medical events that would occur after ICU discharge and that would not be listed in the outcome measures will not be considered as adverse events, since these events cannot be attributed to short-acting insulin.

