## 9.3 Analysis

A Consolidated Standards of Reporting Trials (CONSORT) diagram will be reported.

For the primary and most secondary endpoints taking place during ICU stay, all data will be available. Of the secondary endpoints, some laboratory measurements may be missing. Missing data for one time point may be interpolated, by calculating the mean of the two neighbor measurements. In other cases, missing data will not be imputed.

All analyses will be done on intention to treat basis. In case of request for discontinuation of the study intervention by the patient or legal representative, this will be respected, but all data that are already collected will be analyzed.

The data file will be finalized and locked 90 days after inclusion of the last patient (except for the post ICU follow-up outcome parameters, as specified above). Discrete variables will be summarized by frequencies and percentages. Continuous variables will be summarized by use of either mean and standard deviation (SD) or median and interquartile range as appropriate. Results will be analyzed with the use of Chi-square testing, Student's t test or non-parametric testing (Wilcoxon rank-sum test, Van der Waerden test or Median test), as appropriate. Time-to-event effects will be documented by Kaplan-Meier plots with use of log-rank/Wilcoxon testing; the time-to-event effect size will be estimated with the use of Cox proportional hazard analysis provided the proportional hazard assumption is valid for the dataset. All time-to-event analyses will also be performed on data censored at 90 days. As death is a competing risk for duration of care outcomes, non-survivors will be censored beyond the longest duration of such care required for survivors.

All outcomes will be analyzed in an uncorrected manner as well as adjusted for baseline risk factors (including type and severity of illness, age, gender, body mass index, history of diabetes or not, center). For these analyses, P-values will be considered significant when at or below 0.05 without correction for multiple testing. To assess whether any eventual impact of the intervention on the primary and safety endpoints is affected by the baseline risk factor subgroup, interaction P-values will be calculated (logistic regression or Cox proportional hazard analysis as appropriate) with a threshold for significance of interaction set at a P-value of <0.1. These a

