- Admission date
- Diagnostic group
- Brain injury Y/N and subtype
- Reason for non-inclusion

In the admission file of the CRF, the data on the end of the study will also be included:

- End of study date, time and reason (stopping criteria)
- ICU discharge date (defined as ready to be discharged), ICU length of stay
- Hospital discharge date, hospital length of stay
- Readmission within 48 hours after discharge (Y/N)
- New infection during ICU stay (Y/N), type (bacteremia, airway, urinary tract, wound, other)
- Atrial fibrillation during ICU stay (Y/N) (recorded in selected centers)
- Major Adverse Cardiovascular Event (MACE) during ICU stay (Y/N) (not present on admission / not admission diagnosis) (recorded in selected centers):
  - Non-fatal myocardial infarction (Y/N)
  - Non-fatal stroke (Y/N)
  - Cardiovascular death (Y/N)

- Low cardiac output (Y/N), i.e. cardiac index  $<2.5$  l/min/m^2, need for inotropic support, need for mechanical circulatory support
- Survival outcome:
  - Mortality during hospitalization, Y/N
  - Mortality during ICU stay, Y/N
  - Mortality at day 90 (Y/N), date of death
  - Circumstances of death: therapy withdrawal, refractory shock, brain death
- File completed (Y/N)
- Authorization for completion

Simultaneously, all data from the patient data management system, which are used in routine clinical care, will be kept for the study patients. Additionally, the data that are highly relevant for the study will be included in the CRF on a daily basis:

- Blood glucose values. Only date and time stamped arterial and capillary blood glucose values will be included.
- Hypoglycemia report (will be recorded per hypoglycemic event  $<40$  mg/dl)
  - Minimum blood glucose concentration
  - Maximum blood glucose concentration within 4 hours after correction of hypoglycemia
  - Date and time of hypoglycemia
  - Cause of hypoglycemia
  - Action undertaken
  - Insulin drip decrease/stop (Y/N/no insulin)
  - Bolus glucose (Y/N)
  - Blood glucose concentration  $>40$  mg/dl within 1 hour (Y/N/no value)
  - Immediate consequences (Y/N/unclear)
    - Perspiration (Y/N)
    - Epilepsy within 8 hours (Y/N/Unclear)
    - Severe arrhythmia or shock (Y/N/pre-existing)
    - Death within 24 hours (Y/N) and duration (in hours) from hypoglycemia to death
    - Loss of consciousness (Y/N/sedation)
- All medication given systemically (cumulative daily dose through each route)
- Nutrition

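### Recovery from new kidney injury and the glucose peak after hypoglycemia can be compared only between subsets formed after randomisation, yet the plan tests them as intention-to-treat outcomes

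*Protocol*

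**What the plan says.** Section 3.3 of the protocol puts four kidney items in one bullet: new kidney injury, the "proportion of patients in need of new initiation of renal replacement therapy in ICU", and then "duration of renal replacement therapy in ICU; recovery from kidney injury". The synopsis makes clear that recovery means recovery from injury arising after randomisation: "The presence or absence of new kidney injury during ICU stay, and duration and recovery herefrom".

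The glucose bullet in section 3.3 lists the incidence and number of hypoglycemic events, together with "peak of blood glucose after correction of hypoglycemia; duration of hypoglycemia". Section 13 has a dedicated report, completed for each event below 40 mg/dl, that records "Maximum blood glucose concentration within 4 hours after correction of hypoglycemia". Section 8.1 states: "The main adverse event of the intervention is hypoglycemia, which warrants prompt treatment".

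Section 9.3 states: "All analyses will be done on intention to treat basis". It has all outcomes analysed both unadjusted and adjusted for baseline risk factors, with P at or below 0.05 counted as significant and no multiplicity correction. For duration-of-care outcomes, it censors non-survivors beyond the longest duration seen in survivors. That rule deals with death. It does not deal with selection by occurrence of the event.

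**The concern.** A patient without new kidney injury cannot recover from it, and a patient without hypoglycemia has no peak after its correction. A test of either endpoint therefore compares injured with injured, or hypoglycemic with hypoglycemic. Membership of those groups is decided after randomisation and is an outcome in the same bullet. Randomisation balances the arms. It does not balance these subsets if treatment affects who enters them.

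For hypoglycemia, the protocol itself treats such an effect as a risk of the intervention. For kidney injury, it is one of the questions the trial asks. If tight control prevented mostly mild kidney injury, the injured patients left in that arm would be sicker on average and would recover less often. A nominally significant worse recovery could then be reported although no patient was harmed. If tight control added brief hypoglycemic events, measures averaged over affected patients could look better in the arm that carries the risk.

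**Working it through.** The protocol states no figure to reproduce here. It gives no rates of kidney injury, recovery, renal replacement therapy (RRT) or hypoglycemia. From the document come 9230 patients (section 9.1), 1:1 allocation (section 5.4), hence 4615 per arm, and a 0.05 threshold (section 9.3; two-sided here). **All other inputs below are assumptions.**

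**1. Recovery from kidney injury.** Assume that the control arm has 18% mild injury (80% recover) and 12% severe injury (40% recover). Tight control prevents one third of mild cases, leaving 12%, and changes nothing else.

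- Recovery among the injured, control: (0.18×0.80 + 0.12×0.40)/0.30 = 0.192/0.30 = 64%.
- Recovery among the injured, tight: (0.12×0.80 + 0.12×0.40)/0.24 = 0.144/0.24 = 60%.
- Unresolved injury per randomised patient, control: 0.18×0.20 + 0.12×0.60 = 10.8%.
- Unresolved injury per randomised patient, tight: 0.12×0.20 + 0.12×0.60 = 9.6%.

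The conditional comparison points to harm and the all-randomised one to benefit. In 20,000 simulated trials with a two-proportion z test, worse recovery was nominally significant in 54%. The figure was 21% with one fifth of mild cases prevented and 92% with one half.

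**2. Lower and other assumed rates.** Take 10% mild injury (90% recover) and 5% severe (40% recover), with 30% of mild cases prevented.

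- Among the injured: 0.110/0.15 = 73.3% versus 0.083/0.12 = 69.2%.
- Unresolved per randomised patient: 4.0% versus 3.7%.

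The shift among the injured is again about 4 percentage points, but fewer patients are injured, so the chance of a significant apparent harm is 37% (normal approximation). It is 7%, 18% and 85% with 10%, 20% and 50% of mild cases prevented. With the same recovery rates and 30% prevented:

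| Mild + severe, control | Recovery among injured, control vs tight | Chance of significant apparent harm |
|---|---|---|
| 15% + 10% | 70.0% vs 65.6% | 57% |
| 5% + 5% | 65.0% vs 60.6% | 26% |

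**3. RRT duration, where the denominator is open.** Assume 3% of control patients have a 4-day course and 3% a 14-day course, and that 30% of short courses are prevented.

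- Mean among treated: (0.03×4 + 0.03×14)/0.06 = 9.00 days versus (0.021×4 + 0.03×14)/0.051 = 9.88 days.
- Mean per randomised patient, zero if none: 0.540 versus 0.504 days.

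**4. Hypoglycemia.** Duration is used here because it can be worked both ways. Assume control has 0.5% brief events (30 min) and 0.5% long events (120 min), and that tight control adds 3% brief events.

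- Mean among affected: 0.75/0.01 = 75.0 min versus (0.035×30 + 0.005×120)/0.04 = 41.3 min.
- Mean per randomised patient: 0.75 versus 1.65 min.

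With 1% or 5% added, the tight-arm figures are 52.5 or 37.5 min among affected and 1.05 or 2.25 min per randomised patient. The distortion now flatters the tight arm. The peak after correction is open to the same selection, but no figure is offered for it.

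**The case against.** **The denominator can be left to the SAP.** Section 9.3 promises a full plan before analysis, and an unstated denominator for a secondary endpoint is not an error. This stands for RRT duration and hypoglycemia duration. A reader might infer that these two also exist only in affected patients. The protocol does not say so: it never restricts them, and both can be scored zero in everyone else. It does not stand for recovery and the post-correction peak, where no choice of denominator makes the endpoint, as named, defined for all randomised patients.

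**The true result would be visible next to the misleading one.** Incidence of new kidney injury and of hypoglycemia is listed alongside. In the first scenario, injury falls from 30% to 24%: z = 0.06/√(0.27×0.73×2/4615) ≈ 6.5. A careful reader would see that benefit. This lowers the stakes but does not make the conditional test valid.

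**The sizes are assumed.** This stands. The 54% comes from a high assumed injury rate and no effect on severe injury. A reader might also infer that the intervention is known to change kidney injury. The protocol treats that as a question to be tested.

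**Hypoglycemia may add little.** Section 2 expects the algorithm to remove nearly all of the risk. If the peak is taken from the dedicated report, only events below 40 mg/dl enter, and milder ones do not distort it. Both are fair. Preventing mild cases is also the wrong description for hypoglycemia, where the risk is of added events.

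**Conclusion.** The point holds for two endpoints: recovery from new kidney injury and peak glucose after hypoglycemia. Each is defined only after a post-randomisation event that is itself a trial outcome, so the planned P≤0.05 comparison is not a comparison of the randomised groups, and the intention-to-treat statement does not repair that. The bias arises only if treatment changes who has the event.

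The direction for recovery follows from preventing milder cases: 64% versus 60% among the injured against 10.8% versus 9.6% unresolved per randomised patient, or 73.3% versus 69.2% against 4.0% versus 3.7% at lower rates. How often this would reach significance depends wholly on assumed rates. The documents do not support the stronger readings that all four duration and recovery items suffer from this, that the trial will report false harm, or that the plan prescribes affected-only analyses of RRT duration and hypoglycemia duration. Severity is minor: these are a few items in a long secondary list.

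**What to change.** 1. Replace the tested recovery endpoint by new kidney injury unresolved at ICU discharge, or ICU death (yes/no), in all randomised patients.
2. Analyse duration of RRT in ICU and duration of hypoglycemia per randomised patient, with zero if none. For RRT, apply the protocol's own rule for non-survivors (section 9.3), which section 3.3 already restates for weaning from respiratory and hemodynamic support.
3. Report recovery, RRT duration and post-hypoglycemia peak among affected patients descriptively, without P values, beside the incidence.

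RRT-free days to day 90 would not be a suitable substitute. The RRT endpoint is confined to the ICU, and section 13 lists no RRT data after ICU discharge; only vital status is followed to day 90 in all patients.

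The cost is revised endpoint wording and a little analysis work on ICU data that the present endpoints already need. There are two downsides. The kidney endpoint becomes slightly different because it includes death; the illustrations above do not model deaths. Hypoglycemic time must be read with unequal sampling in mind: intervals of 1 to 4 hours are advised in the tight arm (section 6.1.1) and up to 6 hours in the liberal arm (section 6.1.2), so short events are not equally likely to be detected.
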